### Aims

The primary aim of the study is to determine the temporal association between the community prevalence of HIV viraemia and the incidence of HIV infection among gay and bisexual men at a community-level. The secondary aims are: i) to assess the association between changes in guidelines and policies and earlier uptake of HIV treatment among gay and bisexual men, ii) to identify incidence and predictors of repeat HIV testing among HIV negative gay and bisexual men, and iii) to identify incidence and predictors of supressed HIV viral load among HIV positive gay and bisexual men.

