### Data analyses

TAIPAN will undertake four separate analyses to address the study aims (Table 2).

TAIPAN’s primary aim will be addressed by examining the temporal relationship between community prevalence of viraemia and incidence of HIV infection in gay and bisexual men. For each year of follow up, the community prevalence of HIV viraemia as determined by the calendar year will be entered as an independent variable in the regression. In addition to estimating the effect of community prevalence of viraemia, we will control at the individual level for other demographic, clinical and behavioural determinants of acquisition of new HIV infection, and recent sexual risk practices. We will use random effects Poisson models to undertake multi-level analyses that will allow us to include group-related variables (community prevalence of viraemia), individual variables (demographic, clinical, and behavioural) and time.

The study period will be divided into three-year periods defined by treatment guidelines and policy. The first period will encompass 2009–2011 and serve as a ‘before’ treatment as prevention period. The second period will encompass 2012–2014 and represent a transition period given that several Australian jurisdictions began to expand treatment as prevention initiatives during this time. And the third period will encompass 2015–2017, representing the full implementation of treatment as prevention given that early ART initiation was recommended for both individual and public health purposes. In regards to time lags, we assume that HIV incidence is affected by the estimated prevalence of virological suppression from the preceding year.

The second analysis will examine the temporal relationship between the three time periods described above and the incidence of treatment initiation among men newly diagnosed with HIV (Secondary Aim 1). Using the study periods described above in a regression analysis, incidence of treatment initiation among men newly diagnosed with HIV will be the outcome variable while controlling for clinical, demographic and behavioural factors. Given its historical role in determining when to initiate treatment, CD4 cell count at diagnosis and HIV viral load will also be included in the multivariate model.

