The third analysis will determine incidence and predictors of repeat HIV testing (Secondary Aim 2). To calculate annual estimates we will allocate follow-up time and the incident of repeat testing (i.e., the point at which a second test is achieved) to the calendar year in which it occurs. With this approach it is possible that a patient might achieve multiple incidents of repeat testing in one calendar year. In addition to evaluating changes in the incidence of repeat HIV testing over time, this analysis will employ a regression analysis to identify demographic, behavioural and clinical factors associated with repeat testing incidence among gay and bisexual men in the negative cohort.

The fourth analysis will estimate the incidence of viral suppression among those newly diagnosed and predictors of incidence of viral suppression among the positive cohort (Secondary Aim 3). This analysis will employ Cox proportional hazards regression. Further, we will estimate the median time from diagnosis to first viral suppression by calendar year among those who are diagnosed during the study period, stratified by CD4 cell count at diagnosis. For this analysis and all others, statistical significance will be set at *p* < 0.05.

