### Sample size

Sample size calculations are based on the estimated number of gay and bisexual men diagnosed with HIV annually in New South Wales and Victoria, [6] and assuming a modelling-derived 30% reduction in infections to 420 per year in 2015–2017 (i.e., following the full implementation of treatment as prevention) [22]. For HIV incidence (Primary Aim) an estimated 80% of men diagnosed annually will have some HIV testing history, [23, 24] which equates to 336 incident cases annually and will provide 80% power to detect annual declines in the incidence rate of at least 20% (hazard ratio [HR] = 0.80). Regarding treatment initiation (Secondary Aim 1), assuming a rate of treatment initiation of 36 per 100 person years (unpublished data from Australian HIV Observational Database) and an estimated 420 men newly diagnosed per year, our analysis will have 80% power to detect annual relatives changes in treatment initiation after a new HIV diagnosis of at least 36% (HR = 1.36).

For repeat HIV testing (Secondary Aim 2), it is estimated that 80% of men in the negative cohort will be tested at least once annually for HIV [23, 24] and that 25% will have one further test in the year [25]. If the cohort contains approximately 40,000 men then this translates into 8000 repeat testers annually, which will provide sufficient power to detect at least a 6% annual increase in the incidence of repeat testing (HR = 1.06). And for viral suppression (Secondary Aim 3), if we assume that 90% of newly diagnosed men will start treatment [26] then we will have 80% power to detect a 15% increase in the annual incidence of viral suppression (HR = 1.15). Trend tests over multiple years will have greater power as will combining over multiple years as per the three-year study periods relative to the implementation of treatment as prevention (see Data Analyses).

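### The 80% power labelled for the Primary Aim is for a change in incidence between two calendar years, not for the planned viraemia regression, whose power the document does not give

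*Protocol article*

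**What the plan says.** The Aims section sets the primary aim as to "determine the temporal association between the community prevalence of HIV viraemia and the incidence of HIV infection". Data analyses describes the test: one community viraemia value per calendar year, lagged by one year, is the independent variable in a random effects Poisson model said to "include group-related variables (community prevalence of viraemia), individual variables (demographic, clinical, and behavioural) and time". The significance level is fixed by "statistical significance will be set at *p* < 0.05"; sidedness is not given.

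Sample size starts from "a modelling-derived 30% reduction in infections to 420 per year" in 2015–2017 and takes 80% of diagnosed men as having a testing history. Under the label HIV incidence (Primary Aim), it says that this equates to "336 incident cases annually and will provide 80% power to detect annual declines in the incidence rate of at least 20" per cent, which it gives as a hazard ratio of 0.80. It closes with the remark that "Trend tests over multiple years will have greater power as will combining over multiple years", referring to the three-year policy periods.

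**The concern.** The label and the calculation belong to different hypotheses. The calculation asks whether incidence changed from one year to the next. The primary aim asks whether incidence follows viraemia. Viraemia takes one value per calendar year, so there are at most nine values, or eight pairs once the lag removes 2009. With time in the same model, the viraemia coefficient is informed only by the departure of viraemia from the time term. The annual number of cases does not by itself fix its precision.

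As printed, a reader could take the study to have 80% power for its primary question, and could then give a non-significant time-adjusted viraemia coefficient more weight than it deserves. The closing remark on multi-year analyses adds to that impression.

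**Working it through.** **Inputs from the document.** 420 diagnoses a year in 2015–2017 after a 30% reduction, so 420/0.70 = 600 before. With 80% having a testing history, 0.8 × 600 = 480 incident cases a year before and 0.8 × 420 = 336 after. HR 0.80; alpha 0.05, taken as two-sided; study years 2009–2017; lag one year.

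**1. The stated figure.** Two annual counts with equal person-time: power = Φ(|ln RR|/√(1/d1 + 1/d2) − 1.96), RR = 0.80.

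- 336 then 268.8 cases: z = 2.73, power 77.8%
- 336 in each year: z = 2.89, power 82.4%
- 420 then 336 cases: z = 3.05, power 86.2%

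The stated 80% is therefore a year-on-year comparison of counts, with no viraemia term.

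**2. The powered effect against the assumed effect.** From the middle of 2009–2011 to the middle of 2015–2017 is six years. Evenly spread, 30% is 0.7^(1/6) = 0.942, or 5.8% a year. A 20% decline every year would give 0.8^6 = 0.26, a 74% fall. With 336 then 316.6 cases, z = 0.76 and power is about 12%.

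**3. The multi-year remark.** A crude period comparison has 3 × 480 = 1440 v 3 × 336 = 1008 cases: z = 0.357/√(1/1440 + 1/1008) = 8.7, power above 99.9%. The remark is right for that test.

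**4. The planned coefficient, under assumptions.** The document does not give the viraemia path, the form of time or the between-year variation. Assume linear time, constant person-years, and incidence in 2010–2017 on viraemia v in 2009–2016 (0 = start level, 1 = end level). Then ln μ = a + b·v + c·year, with c = 0 as the true value. SE(b) is the square root of the v-element of (XᵀWX)⁻¹, where W has diagonal 1/(1/μ + s²) and s is the between-year SD on the log scale. Power = Φ(|b|/SE − 1.96). For each path, b is set so that expected cases average 480 in 2010–2011 and 336 in 2015–2017.

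| Assumed path of v, 2009–2016 | b | SE (s = 0) | Power, s = 0 | s = 0.03 | s = 0.05 |
|---|---|---|---|---|---|
| 0, 0, 0, ¼, ½, ¾, 1, 1 | −0.390 | 0.158 | 69.8% | 55.4% | 40.1% |
| 0, 0, 0, 1/6, ½, 5/6, 1, 1 | −0.378 | 0.133 | 81.3% | 67.5% | 50.5% |
| 0, 0, 0, ½, ½, ½, 1, 1 | −0.434 | 0.135 | 89.5% | 78.3% | 61.6% |
| (t/7)², t = 0 to 7 | −0.490 | 0.190 | 73.1% | 59.8% | 44.5% |
| 0, 0, 0, 0.2, 0.4, 0.6, 0.8, 1 | −0.449 | 0.180 | 70.3% | 55.7% | 40.2% |
| 0, 0, 0, 1/3, 2/3, 1, 1, 1 | −0.357 | 0.126 | 81.1% | 67.9% | 51.4% |

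The last row worked through: expected cases 480, 480, 480, 426, 378, 336, 336, 336; 0.357/0.1255 = 2.84; Φ(2.84 − 1.96) = 0.81.

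**5. Outside these six paths (s = 0).** For a straight-line decline the coefficient is not estimable alongside linear time. For logistic declines v = 1/(1 + exp(−k(t − 3.5))), power is 32% at k = 1 (R² with time 0.97) and 15% at k = 0.7 (R² 0.99). For a single step it is about 100%. Without a time term it is about 100% for every path. With indicators for the three periods instead of linear time, a separate calculation on nine annual counts falling from 480 to 336 gives 59–90% for gradual declines, and no estimate for steps at the period boundaries.

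**The case against.** The sentence speaks of declines in the incidence rate, and Table 2 lists HIV incidence as an outcome indicator for the primary aim; read literally, it claims nothing about a viraemia coefficient. The arithmetic is sound. The 30% reduction serves to fix the case count, HR 0.80 is a smallest detectable year-on-year change, and the plan itself points to pooling. The form of time may properly be left to a fuller document.

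Much of this stands. There is no arithmetic error, the 12% in step 2 does not describe the study's ability to detect a fall in incidence over the whole period, and not stating the form of time is not the fault raised here. But Table 2 lists viraemia prevalence beside incidence, and the aim is the relation between them. A figure labelled for the Primary Aim that contains no viraemia quantity is a figure for another test.

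A reader might go further and infer that the planned model is underpowered at the plan's own 30% effect, at about 50–77%. The document does not support this. Values of 49–77% arise for the first five paths in the table if the 30% reduction is placed only at the end of the path. Those paths then average 343–368 cases in 2015–2017, not the 336 the plan assumes. Set to 336, the same five give about 70–90%, on both sides of 80%. Any such band also rests on an assumed viraemia path and form of time.

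**Conclusion.** The mismatch is real. The 80% is the power for a 20% change in incidence between two calendar years with about 336 cases a year, and it is not the power of the primary analysis. The detectable 20% annual decline is also far from the roughly 5.8% a year implied by the plan's own assumption if evenly spread.

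How much power the planned coefficient has cannot be settled from the document. About 70–90% holds for six assumed non-linear paths with linear time, constant person-years and pure Poisson error. Between-year variation of 0.03 to 0.05 on the log scale lowers this to about 40–78%. The full range over the paths considered runs from not estimable to near 100%. The conclusion is that the stated figure does not answer the primary question, not that the study is shown to be underpowered for it. Viraemia values that differ by state would add some information, but the document describes viraemia by calendar year only.

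**What to change.** Three changes under Sample size:

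- Relabel the 336-case figure as power for a year-on-year change in incidence, and say that it does not apply to the Primary Aim's viraemia association.
- Give the power, or the smallest detectable rate ratio per unit of viraemia, for the planned model with lagged annual viraemia and time. A short simulation over stated viraemia paths, with a stated form of time, is enough. Treat the 30% reduction as a 2015–2017 average, and include at least one near-linear path and some between-year variation.
- Limit the remark on greater power to incidence trends and period comparisons that are not adjusted for time.

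The cost is a short simulation and one reworded paragraph, with no more patients or data. The stated power for the primary question may become less favourable.

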**Fig. 1 Fig1:**
[figure not shown]
Method for calculating the prevalence of HIV viraemia among diagnosed and undiagnosed gay and bisexual men

#### Outcome 2

HIV incidence will be calculated using repeat testing among the negative cohort, [18] which will consider patients with two or more HIV tests for whom the first test was negative. We expect that more than 80% of gay and bisexual men will have at least two tests over the study period. An incident infection will be defined as an HIV diagnosis following a negative test and time at risk will be calculated as the time between each patient’s first and last test or a patient’s first test and HIV diagnosis. The number of incident infections will be divided by the person time (in years) at risk.

#### Outcome 3

Data from the positive cohort will also be used to calculate the incidence of ART initiation (i.e., the point at which ART is initiated) with the follow-up period defined as the time after HIV diagnosis (person years of infection). This variable will be restricted only to men diagnosed with HIV during the study period.

#### Outcome 4

Data from the negative cohort will be used to calculate the incidence of repeat diagnostic HIV testing. The incident event is defined as the point at which a patient achieves a second HIV test within six weeks to 12 months of a previous test, with follow-up time defined as the period between a patient’s first HIV test and last clinical encounter. Follow-up time will cease if a patient has no recorded service event of any kind within a two year period but will resume at the point of future service events (i.e., reengages with a participating service). Follow-up will also cease if a patient is diagnosed with HIV.

#### Outcome 5

Among the positive cohort, the incidence of viral suppression will be calculated. Viral suppression is defined as two consecutive viral load tests of <200 RNA copies/mm^3^ separated by at least three months; the first test will be taken as the point of suppression for calculating time. This variable will only be calculated among patients with no history of previous treatment and will exclude those for whom there is no or only one viral load test result. We will conduct a sensitivity analysis with a higher viral load threshold of <1000 RNA copies/mm^3^.

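### The stated 80% power for a 15% annual rise in viral suppression (HR 1.15) does not follow from the plan's own inputs, which give about 50% power and a detectable HR of about 1.22

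*Protocol article*

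**What the plan says.** The Sample size section builds its calculations on annual new diagnoses in the two states, "assuming a modelling-derived 30% reduction in infections to 420 per year in 2015–2017". For viral suppression it adds one further input, "if we assume that 90% of newly diagnosed men will start treatment", and concludes that there will be "80% power to detect a 15% increase in the annual incidence of viral suppression", given as HR 1.15. It states no event count, baseline rate or follow-up time for this aim.

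Three other places bear on the figure:

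- The Data analyses section names Cox regression for this aim and fixes the 5% level across the study ("For this analysis and all others, statistical significance will be set at" p < 0.05). It does not say whether tests are one- or two-sided.
- Outcome 5 counts a man as suppressed after two consecutive results below 200 copies at least three months apart, and "will exclude those for whom there is no or only one viral load test result".
- The last sentence of Sample size says that trend tests and pooling over the three-year periods will have more power. The quoted 80% is therefore for one year against another.

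For the primary aim the same section gives a comparable statement with its event count: "which equates to 336 incident cases annually and will provide 80% power to detect annual declines in the incidence rate of at least 20" per cent (HR 0.80).

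**The concern.** Under a Cox model, power for a given HR depends on the number of events. The suppression sentence allows 378 men a year (0.90 × 420), only 12.5% more than the 336 annual events behind the primary aim. Yet the claimed detectable effect shrinks from HR 0.80 to HR 1.15, or from 0.223 to 0.140 on the log scale. Precision grows with the square root of the event count, so 12.5% more events cannot buy that gain.

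At stake is how an annual comparison for Secondary Aim 3 will be read. A reader who trusts the stated power would take a null result as evidence against a 15% improvement, when the study would miss such an improvement about half the time.

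**Working it through.** **Inputs**

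- New diagnoses per year, 2015–2017: 420 (Sample size).
- Share starting treatment: 90% (Sample size), so 0.90 × 420 = 378 men. Each contributes at most one first suppression. The viral-load requirements in Outcome 5 can only lower this.
- Significance level: 0.05 (Data analyses), taken as two-sided; one-sided is also shown.
- Comparison: one year against another.

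**Formulas**, with d1 and d2 the events in the two years:

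- SE(log HR) = √(1/d1 + 1/d2)
- Power = Φ(|ln HR| / SE − 1.96)
- HR detectable at 80% = exp(2.80 × SE), where 2.80 = 1.96 + 0.84
- Events needed per year, equal years = 2 × 7.85 / (ln HR)²

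**Step 1: check the method on the plan's own figures**

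- Primary aim, 336 v 336 events, HR 0.80: SE = √(2/336) = 0.0772; 0.2231/0.0772 = 2.89; power = Φ(0.93) = 82%. The detectable HR is 0.806. If the second year has 20% fewer events (336 v 269), power is 78%. The stated 80% is reproduced.
- Treatment initiation: taking 36 per 100 person-years over 420 person-years gives 151 events, and 151 × 1.36 = 206 in the comparison year. Power at HR 1.36 is 82% (76% with 151 in both years). This agrees with the stated 80%. It serves only as a check of the method.
- Repeat testing, 8,000 v 8,000, HR 1.06: 96%, consistent with the claim there of sufficient power.

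**Step 2: viral suppression, HR 1.15 (ln HR = 0.1398)**

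- Equal years, 378 v 378: SE = √(2/378) = 0.0727; 0.1398/0.0727 = 1.92; power = Φ(−0.04) = 48.5%.
- Second year 15% higher, 378 v 435: SE = 0.0703; power = Φ(0.03) = 51.1%. This is generous, since 435 exceeds all 420 diagnosed men.
- HR detectable at 80%: exp(2.80 × 0.0727) = 1.226 with equal years, 1.215 with growing events.
- Events needed for HR 1.15: 2 × 7.85 / 0.1398² ≈ 804 in each year, against 378 available.

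Scaling the primary-aim figure directly gives the same answer: 0.2231 × √(336/378) = 0.2104, and exp(0.2104) = 1.23.

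**Step 3: more favourable readings**

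| Reading | Power at HR 1.15 |
|---|---|
| 378 a year, one-sided 5% | 61% |
| All 420 diagnosed men reach suppression | 53% |
| Before the 30% reduction: 420/0.70 = 600 diagnoses, 540 starters | 63% |
| All 600 earlier diagnoses counted as events | 68% |
| One year at 540, the other at 378 | 55% |
| Three-year periods, 3 × 378 = 1,134 in each | 91% |

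Only the pooled contrast passes 80%, with a detectable HR of exp(2.80 × √(2/1,134)) ≈ 1.12–1.13. The plan presents pooling as power beyond the stated figure.

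**The case against.** The strongest counter-argument concerns the event count. Outcome 5 is not limited to men diagnosed during the study. It admits positive-cohort patients with no previous treatment, and Data analyses places the predictor analysis in the positive cohort as a whole. Treatment-naive men diagnosed before 2009 could therefore add events. As an illustration only: if 27% of the 13,000-man cohort were untreated (100% minus the 73% coverage given in Background), that is 3,510 men. The missing 804 − 378 = 426 events would then need about 12% of them to reach suppression in a year. This stands as far as it goes: 378 is a ceiling only for the group the power sentence names, and a reader should not take it as a limit on the whole analysis. But the sentence counts only newly diagnosed men and offers no other number, so the stated 80% still cannot be obtained from it.

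Other routes come near 80% but do not fit. Treating the earlier year's rate as known gives 78% with 378 events, but would give 98% for the primary aim. Comparing proportions gives 79% if the baseline is 0.63, a value the plan does not state, and the result would not be a Cox HR.

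A reader might also infer two stronger points that the document does not support:

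- That 90% starting treatment (Secondary Aim 3) contradicts "assuming a rate of treatment initiation of 36 per 100 person years" (Secondary Aim 1). The 90% has no time horizon, and a constant annual rate can reach 90% eventually. Nor can that rate be used to cap annual suppression events at first-year starters, because men from earlier diagnosis years remain at risk.
- That suppression cannot be better powered than treatment initiation, which is powered for HR 1.36. The two outcomes have different eligible men (Outcome 3 is restricted to diagnoses in the study period) and different event counts.

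Finally, this is a secondary aim in a study of routinely extracted records. No recruitment target depends on the figure, and a null result should be judged by its confidence interval. That limits the severity but does not make the figure right.

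**Conclusion.** The stated power is wrong as written. On the plan's inputs, an annual comparison has about 48–51% power at HR 1.15, and 80% power is reached at an HR of about 1.22 (1.215–1.226). With 378 events in each year, an observed HR of exactly 1.00 would carry a 95% interval of about 0.87 to 1.15 (exp(±1.96 × 0.0727)), so it would not clearly exclude the 15% increase.

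This rests on two-sided 5% testing, one year compared with another, and events drawn only from the newly diagnosed men the sentence names. The 540 starters a year implied for earlier years raise power only to about 63%. The document does not show how HR 1.15 was obtained.

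The finding does not mean that Secondary Aim 3 is underpowered in every analysis: the three-year contrast has about 91% power at HR 1.15. It should be corrected, but it is not critical to the study.

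**What to change.** In the Sample size section, do one of the following for Secondary Aim 3:

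- state 80% power for an annual HR of about 1.22, based on at most 378 events a year; or
- give the figure for the three-year contrast, an HR of about 1.13 with 1,134 events per period, and say that it refers to that contrast; or
- if treatment-naive men diagnosed earlier are meant to contribute, state the annual event count that supports HR 1.15 (about 804 in each year) and where those events come from.

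State also that the test is two-sided, if it is. The cost is a less favourable published figure under the first option; data collection and analysis do not change.
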